### Total Knee Replacement Platform Technology

The design and functionality of the TKR platform have been informed through a user needs analysis. The user needs analysis (paper forthcoming) included interviews and focus groups with patients (n=11), general practitioners (n=8), orthopedic surgeons (n=12), and physiotherapists (n=3). The results of the analysis from the qualitative data clearly identified different stages of the TKR journey, each with different needs and priorities, which has informed the design of our platform technology for TKR. The qualitative data was used to refine features and functionalities of the platform, which comprises a patient facing app and activity tracker and a clinical Web portal for use by clinical care teams.

The information delivered via the app been scientifically validated and all exercise videos were created in conjunction with expert physiotherapists working with TKR patients.

In order to foster motivation, the purpose-built app for iOS and Android devices includes weekly psychoeducation sessions and tasks that are delivered by a program guide via text and voice recordings. This content is also reinforced through tasks (eg, goal-setting) that the user can complete outside of the app (eg, on paper). This motivational content was developed using self-determination theory [19] and included techniques designed to foster positive emotions [20]. Tools to assist in behavior change in the app use commonly identified behavior change techniques, such as self-monitoring, goal setting and reviewing, and rewarding/recognizing achievements that appear in various behavioral models which can be broadly encompassed by social cognitive theory [21,22].

The clinical Web portal is designed for clinicians to monitor patient progress and configure physiotherapy programs. Patient data, gathered by the app, is transmitted to the portal for review by members of a patient care team. Physiotherapy programs for each patient are configured from a library of videos typically used for TKR rehabilitation. Once set, programs are available to patients in their app. Figure 1 provides sample screenshots of the TKR platform.

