**Patient self-report**						
	Knee	OKS^a^	x	x	x	x
	Quality of life	SF-36^b^	x	x	x	x
	Depression, anxiety, stress	DASS21^c^	x	x	x	x
	Clinical satisfaction	Trial specific questionnaire			x	
	Service delivery satisfaction	Trial specific questionnaire		x	x	
	Technical satisfaction	Trial specific questionnaire			x	
	Self-motivation	SMI^d^		x		
	Self-determination	SDQ^e^		x		
	Self-efficacy	SES^f^	x	x	x	x
	Economic	Patient diary			x	

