#### Secondary Outcomes

The secondary outcomes include:

Quality of life (RAND 36 Item Short-Form Health Survey [SF-36]): SF-36 is a 36-item questionnaire that will be used for constructing summary scores of physical and mental components [24]. The questionnaire assesses 8 domains of wellness through subscales including body pain, physical function, general health, mental health, social functioning, and emotional role. The SF-36 is a popular instrument in the knee domain to measure generic quality of life [25].Knee range of motion (ROM): A long-arm goniometer will be used for measuring the knee ROM (flexion and extension) [26]. The goniometer axis will be positioned over the lateral knee joint area and the arms will be aligned with the lateral malleolus using the greater trochanter. The active knee flexion will be measured in the sitting position and the active knee extension will be measured in the long sitting or supine position. ROM as part of week 12 will be collected during the patients’ follow-up clinical visit, typically 6 weeks following surgery.The Depression, Anxiety and Stress Scale (DASS21) will be used to measure mental well-being. This is a 21-item questionnaire using a 4-point Likert scale with 7 items per condition (depression, anxiety, stress) [27]. Each item has equal weighting (0 to 3) and a higher score indicates greater symptoms. While SF-36 covers general mental health (psychological distress and psychological well-being), DASS21 is specifically designed to measure negative emotional states and severity of feelings related to depression, anxiety, and stress and has proven to be sensitive to patients’ response to treatment.Satisfaction with knee surgery and service delivery (prehabilitation, rehabilitation) and the use of technology (eg, app and wearable) will be measured with questionnaires developed by the Commonwealth Scientific and Industrial Research Organization (CSIRO) using a 5-point Likert scale. The questionnaires are designed to capture surgical results, surgical recommendations, interaction with clinicians, empowerment experience, observability, and overall satisfaction with the service delivery. The technical satisfaction questionnaire will capture complexity, compatibility factors, and experience with the app and the wearable.Self-motivation will be captured using a validated 40-item scale [28] called the Self-Motivation Inventory (SMI). It has been used previously to assess rehabilitation outcomes for anterior cruciate ligament reconstruction [29]. The scale captures 10 areas of self-motivation and could be a critical predictor of adherence to a rehabilitation program. Therefore, we will be capturing this to control for any confounding effects that this may have on the experimental conditions.Self-determination will be captured using a 4-item questionnaire in order to assess whether the intervention group has higher levels of autonomous and/or intrinsic motivation after the presurgery phase (ie, week 0). In line with methods of Sheldon and Kasser [30], participants will be asked to rate 4 reasons for pursuing the goal of successful rehabilitation according to how much each describes their reason for having this goal. These reasons cover the proposed spectrum of possible motivations from external to introjected to autonomous to intrinsic, all derived from self-determination theory. All responses are rated from 1 (not at all because of this reason) to 9 (completely because of this reason).Self-efficacy to perform rehabilitation activities is a critical predictor of rehabilitation success. It describes a person’s confidence in their ability to perform certain behavior in the face of challenges. In order to capture changes in self-efficacy, we will be using an adapted version of a physical activity Self-Efficacy Scale (SES) [31] designed to ask these questions around rehabilitation physiotherapy exercises rather than general exercise intention. This is a 5-item questionnaire using a 4-point Likert scale.

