### Statistical Analysis

Statistical data analysis will be performed using an intention-to-treat approach. Mixed model analysis will be used for continuous variables (primary and secondary outcomes) measured at week 0, week 12, and week 52 for those receiving the TKR platform compared with usual care by time effects. Fixed effects will be included for the intervention, the time points, and the interaction between the 2 variables. These models will also account for relevant covariates such as baseline (4 weeks before surgery) measures, participant sex, baseline levels of motivation, etc. These covariates will be entered as fixed effects. Due to potential confounding effects between different hospitals, these will be also assessed in the mixed model as random effects. Sensitivity analysis will be used to assess the impact of these covariates before the final model is constructed. Other outcome measures of app usage, self-management (eg, physical activity), and compliance with the program (eg, physiotherapy exercise) will be analyzed using logistic or conditional logistic regression to adjust the comparisons for other variables for categorical or ordinal variables and multiple regression for continuous variables. All statistical analysis will be done using Excel (Microsoft Corp), R (R Foundation), or SPSS (IBM Corp).

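### The efficacy models adjust for baseline motivation, but Table 1 first measures motivation at week 0, after about 4 weeks of a motivational app, so the adjustment may bias the OKS comparison

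*Protocol article*

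**What the plan says.** The Statistical Analysis section plans an intention-to-treat analysis with mixed models for "continuous variables (primary and secondary outcomes) measured at week 0, week 12, and week 52". On covariates it states: "These models will also account for relevant covariates such as baseline (4 weeks before surgery) measures, participant sex, baseline levels of motivation, etc". It adds: "These covariates will be entered as fixed effects". The same sentence that names motivation fixes the meaning of baseline: "baseline (4 weeks before surgery) measures".

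In Table 1 the row "Self-motivation" (SMI) has one mark, in the week 0 column, and so does the self-determination row (SDQ). Both baseline cells are empty. The OKS and self-efficacy rows are marked in all four columns, so the columns have survived extraction.

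The Secondary Outcomes section gives the two instruments different roles. Of the SMI, which it calls a possible predictor of adherence, it says: "Therefore, we will be capturing this to control for any confounding effects that this may have on the experimental conditions". The SDQ is there to test whether the intervention group "has higher levels of autonomous and/or intrinsic motivation after the presurgery phase (ie, week 0".

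The Overview and Aims and Intervention sections start the app about 4 weeks before surgery. The section on the platform technology describes weekly psychoeducation intended to build motivation: "This motivational content was developed using self-determination theory [19] and included techniques designed to foster positive emotions [20".

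**The concern.** The model asks for a motivation value from 4 weeks before surgery, and the schedule collects none. Followed literally, the covariate cannot be fitted. Followed in practice, a week-0 score enters under a baseline label.

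A week-0 score is taken after randomisation and after about 4 weeks of treatment that targets motivation. Conditioning on it has two consequences. Any part of the effect on OKS that runs through motivation is taken out of the treatment coefficient. And where an unmeasured factor affects both week-0 motivation and OKS, the arms are no longer comparable at a given motivation score, which can bias the estimate either way. The week-0 visit is the most exposed: OKS at that visit is one of the modelled outcomes and is measured alongside the covariate, so knee status may itself drive the motivation score.

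At stake is whether the primary coefficient estimates the effect of assignment, as the intention-to-treat statement implies.

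**Working it through.** **1. Timing, side by side (protocol article).**

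| Item | Where | Time |
|---|---|---|
| Covariate named in the model | Statistical Analysis | baseline, 4 weeks before surgery |
| App and tracker issued | Overview and Aims; Intervention | about 4 weeks before surgery |
| SMI collected | Table 1 | week 0 only |
| SDQ collected | Table 1 | week 0 only |
| Group difference in SDQ tested | Secondary Outcomes | week 0 |

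The self-efficacy scale does have a baseline value, but it measures a different construct.

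**2. The plan's own sample size.** Inputs from the Sample Size section: 80% power, P=.05 (taken as two-sided), difference 0.15, SD 0.5, correlation 0.5, baseline plus 3 repeated measures (m = 4), 20% loss.

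- Variance factor for the mean of m measures: (1 + (m − 1)ρ)/m = (1 + 3 × 0.5)/4 = 0.625.
- n per arm = 2 × (0.5/0.15)² × (1.960 + 0.842)² × 0.625 = 109.0, which rounds up to 110.
- Total 220; 220 × 1.2 = 264, against 262 stated.

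The other eight cells of Table 2 come out within 3 participants by the same route. The sizing model is therefore reproduced, with about 262/1.2/2 = 109 evaluable per arm.

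**3. Effect after adjustment.** Planned effect in SD units: 0.15/0.5 = 0.30, taken as an improvement. Suppose the app shifts week-0 motivation by *a* SD and OKS changes by *b* SD per SD of motivation. Under linear mediation:

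adjusted effect = 0.30 − a × b; share lost = a × b / 0.30.

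The documents give neither *a* nor *b*; both are assumptions. Power is at 109 per arm. The variance is 0.625 with no credit for the covariate, and 0.625 − b² with credit.

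| a | b | Adjusted effect (SD) | Lost | Power, no credit | Power, with credit |
|---|---|---|---|---|---|
| 0 | 0.3 | 0.30 | 0% | 80% | 86% |
| 0.1 | 0.1 | 0.29 | 3% | 77% | 78% |
| 0.2 | 0.3 | 0.24 | 20% | 61% | 68% |
| 0.3 | 0.3 | 0.21 | 30% | 50% | 56% |

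The planned model without motivation has 80% power.

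**4. Check by simulation** (n = 400,000; effect 0.30, a = 0.3, b = 0.3). The estimated treatment effect is 0.299 unadjusted, 0.299 adjusted for pre-treatment motivation, and 0.209 adjusted for week-0 motivation. The distortion comes from when motivation is measured; adjusting for motivation is not in itself the problem.

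**The case against.** Several points on the other side have weight.

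- **The expected week-0 difference is stated for the SDQ, not the SMI.** This stands. The SMI is the scale earmarked for adjustment, and no sentence predicts that the app moves it. A shift is plausible, because the app is built to raise motivation, but it is an inference.
- **The loss may be nil.** This also stands. If the app does not move the motivation score, nothing is lost through mediation, and the covariate may even add precision. A reader might infer that the adjustment necessarily removes part of the treatment effect; the documents do not support that.
- **The timing of the SMI rests on one table cell.** The text gives no time for it, and Figure 2, which shows the timeline, is not available here. The cell could be the error and the word baseline in the model correct. What is certain is that the two places conflict.
- **The covariate list is open-ended, and a sensitivity analysis precedes the final model.** So a reader should not conclude that the primary result will fail to be an intention-to-treat effect; that depends on whether the covariate is kept. But motivation is named outright, its purpose is stated under Secondary Outcomes, and checking a covariate's influence does not turn a week-0 score into a baseline one. Nor can an analysis plan supply a measurement that was not taken.

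**Conclusion.** The point holds as an internal contradiction. The model calls for motivation at 4 weeks before surgery, and the schedule provides it only at week 0, after treatment has begun. As scheduled, the covariate is post-randomisation and a plausible mediator, and adjusting for it may bias the OKS comparison and those for the secondary outcomes.

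The likely direction is toward no effect if the app works through motivation; unmeasured common causes could push it either way. The size cannot be fixed from the documents. Over the assumed values above, the mediated loss runs from 0% to 30% of the planned 0.30 SD effect. At the upper end, power falls from 80% to about 55% (50% without and 56% with credit for the variance that the covariate explains). These figures rest on linear mediation, a two-sided test, no unmeasured common cause, and the plan's own sizing model.

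**What to change.** 1. Reconcile the Statistical Analysis section with Table 1 on when motivation is measured.
2. Leave week-0 SMI and SDQ out of the primary and secondary efficacy models for all participants. One model cannot carry the covariate for some participants and not for others. Use the week-0 scores only as outcomes or in a separate mediation analysis.
3. State that no variable measured after randomisation enters the efficacy models as a covariate.
4. If adjustment for motivation is still wanted, collect the SMI at the existing baseline visit before the app is issued. The Results section reports that the first site began in October 2016, so participants already enrolled may have no such value. Adjustment for baseline SMI therefore belongs in a secondary analysis limited to participants who have it.

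Cost: two or three sentences of protocol text. Dropping motivation from the models has no other cost. Item 4 adds a 40-item questionnaire at the baseline visit.

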#### Primary Outcome

The primary outcome measure is self-reported knee pain and function as measured by the Oxford Knee Score (OKS) [23]. The OKS is 12-item questionnaire with 5 items for assessing pain and 7 for assessing function, each with 5 categories of response. Each item is scored from 1 to 5, from least to most difficulty or severity. A single combined score ranges from 12 (ie, least difficult) to 60 (ie, most difficult), and a lower score indicates a better outcome. The OKS has been developed and validated to specifically assess function and pain after TKR and is widely used by clinicians.

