### Sample Size

The sample size is calculated based on the primary outcome (ie, OKS), by considering 80% power (*P*=.05) with a 15% difference in the control group and the intervention group. The standard deviation within each group in the TKR trials can vary based on factors such as number of trial sites (eg, single-center vs multicenter) and heath care cover (eg, public patients vs private patients). Furthermore, in a repeated measure scenario or when considering multiple assessments within a trial (eg, baseline, prehabilitation, 12 weeks rehabilitation, 12 months free living), the correlation among repeated measures needs to be considered as well. Based on these factors the sample size is presented in Table 2 for a variety of scenarios. A low subject variation can be expected with participants when considering only 1 trial site or 1 type of health care cover (eg, public), and a high variation can be expected when participants are mixed. A high correlation in repeated measures can be expected for patients with big differences in the outcome measure within the assessment points.

**Table 2 table2:** Estimated sample size (with 20% loss) based on standard deviation (SD) within groups and correlation among baseline and 3 repeated measures [80% power, *P*=.05, 15% difference].

SD within group/ correlation repeated measure	Low repeated correlation (SD 0.2)	Mid repeated correlation (SD 0.5)	High repeated correlation (SD 0.8)
Low subject variation (SD 0.2)	31	46	60
Mid subject variation (SD 0.5)	170	262	360
High subject variation (SD 0.8)	432	674	914

We estimate that a total of 262 patient participants would be sufficient for this study; however, we expect a maximum of 320 participants from the 5 trial sites based on their rate of TKR surgeries during the trial timeline. A minimum sample size of 100 is suggested for using OKS as the primary outcome measure [33]. Based on the literature [1,7,34], 80% power (*P*=.05) with a 15% difference in the control group and the intervention group has been reported for primary outcome measure.

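### The final OKS model is built after covariate impact is assessed and no decisive contrast is named, so the 5% level is not protected; Table 2 sizes a different quantity

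*Protocol article*

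**What the plan says.** The protocol article makes the Oxford Knee Score (OKS) the primary outcome and schedules it at four times: baseline (about 4 weeks before surgery), week 0 (immediately before surgery), week 12 and week 52. The Primary Outcome section attaches no visit to it.

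The Statistical Analysis section fits a mixed model to weeks 0, 12 and 52. On its terms it says: "Fixed effects will be included for the intervention, the time points, and the interaction between the 2 variables". It describes the comparison with usual care in terms of time, which leans towards the interaction, but it does not say which term or visit decides the trial. The covariates are given as examples (baseline measures, sex, baseline motivation) and the list is left open. Then: "Sensitivity analysis will be used to assess the impact of these covariates before the final model is constructed".

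The Sample Size section works "by considering 80% power (*P*=.05) with a 15% difference in the control group and the intervention group", and the caption of Table 2 refers to "correlation among baseline and 3 repeated measures". The chosen cell is 262, with an expected maximum of 320. Overview and Aims calls the trial unblinded.

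**The concern.** Assessing covariate impact first and fixing the model second lets the data shape the primary model. If whoever does this can see how each covariate set moves the treatment estimate, the choice can follow the result. The unnamed contrast widens the choice.

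The candidate tests also answer different questions. With baseline as a covariate, the interaction asks whether the effect differs between weeks 0, 12 and 52, while the average over those visits is diluted by week 0 if benefit comes only after surgery. The sample size could have shown which quantity was meant, but it describes one that the analysis model does not estimate. What is at stake is whether a significant OKS result can be read as confirmatory.

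**Working it through.** **1. Reproduce Table 2.** Inputs from the Sample Size section: difference 0.15, SD 0.5, correlation 0.5 (the middle column, read as a correlation), 80% power, 5% taken as two-sided, and 20% loss.

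One measure: n per arm = 2 × (1.96 + 0.842)² × 0.5² / 0.15² = 174.4, so 175.

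Average of four equally correlated measures: variance factor (1 + 3 × 0.5)/4 = 0.625. Then 174.4 × 0.625 = 109.0 per arm, rounded up to 110, so 220 in total, and 220 × 1.2 = 264. The stated figure is 262 (without rounding up: 218.0 × 1.2 = 261.6).

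The same quantity computed with the noncentral F distribution matches the whole table closely:

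| SD | Correlation 0.2: computed / stated | 0.5 | 0.8 |
|---|---|---|---|
| 0.2 | 31.2 / 31 | 45.6 / 46 | 60 / 60 |
| 0.5 | 170.4 / 170 | 264 / 262 | 360 / 360 |
| 0.8 | 432 / 432 | 674.4 / 674 | 914.4 / 914 |

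For the chosen cell, averaging three measures gives 281, and inflating by 1/(1 − 0.2) gives 275; neither fits. Table 2 therefore sizes a group effect averaged over baseline and three follow-ups, although no effect can exist at baseline. The analysis model takes baseline out of the average and uses it as a covariate.

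**2. What the choice of contrast does to N.** Same inputs, equal correlations of 0.5, × 1.2 for loss, starting from 350 for one unadjusted visit:

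- Week 12 alone, unadjusted: 350 × 1.2 = 420.
- Week 12 alone, adjusted for baseline: 350 × (1 − 0.5²) × 1.2 = 315. At correlation 0.2 this is 350 × 0.96 × 1.2 = 403; at 0.8 it is 350 × 0.36 × 1.2 = 151.
- Three-visit average, adjusted, same effect at every visit: factor (1 + 2 × 0.5)/3 − 0.5² = 0.417; 350 × 0.417 × 1.2 = 175.
- The same average with no effect at week 0: the mean difference falls to 0.10, so 175 × (0.15/0.10)² = 394.

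The stated 262 corresponds to none of these.

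**3. False-positive rate with no true effect.** Simulated with baseline-adjusted OKS at weeks 0, 12 and 52. At correlation 0.5 the adjusted visits correlate (0.5 − 0.25)/(1 − 0.25) = 0.333.

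- Any one test fixed in advance (a visit, the average or the interaction): 4.8–5.3%.
- Any of the three visits: about 13% (12.9–14.3% over correlations 0.2 to 0.8; bound under independence 1 − 0.95³ = 14.3%).
- Average or interaction: 9.5–9.9%.
- Any visit, the average or the interaction: about 16% (15.8–16.8%).

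**4. Covariate choice alone.** The article gives no correlations, so these are assumed: four covariates correlated 0.5 (baseline OKS), 0.3, 0.15 and 0.15 with OKS, N = 210 (262 × 0.8), 8,000 simulated trials. A fixed full model gives 4.9%. The smallest p-value over the 8 sets that keep baseline OKS gives 8.4%. If baseline OKS may also be dropped (16 sets), it is 12.1%.

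**5. The motivation covariate.** The Statistical Analysis section adjusts for baseline motivation. Table 1 collects the Self-Motivation Inventory (SMI) only at week 0, about 4 weeks after the intervention starts. It is therefore a post-randomisation measure that the app, with its motivational content, may already have changed.

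**The case against.** The strongest defence is that this is a condensed article and an SAP may exist. Naming the primary visit, the contrast and any multiplicity rule is commonly left to an SAP, and listing the terms of a mixed model does not make each of them primary. That stands: the missing visit alone would not be a finding. It matters here because it comes with a stated model-building sequence and a sample size for another quantity.

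Second, the covariate sentence does not say impact on the treatment comparison, nor that arms are revealed. Impact on fit or variance is a natural reading, and unblinded describes the trial design. That also stands as a limit. A reader might infer that the sponsor plans to pick the model by its treatment effect; the article does not say so. It says only that the assessment comes first, and offers no safeguard.

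Third, the text says the models will account for baseline and enter the covariates as fixed effects. The 12% figure, which lets baseline OKS be dropped, therefore goes beyond the text; 8% is the fairer one.

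Two further readings are tempting. One is that the interaction cannot detect a constant benefit, so the trial would miss it. The interaction's 5% detection rate there is true by construction, and the same model contains the intervention effect, which can detect it. The other is that the trial is underpowered. Depending on the contrast and where the effect lies, 262 is more than enough or too few.

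**Conclusion.** The point holds in a limited form. The order of work is stated, so it is not mere silence, and it leaves the 5% level unprotected. It would be wrong to say that 5% fails: each single prespecified test holds it, and inflation arises only if the test or the covariates are chosen after seeing results. A covariate review blind to arm, or an SAP fixed before unblinding, would avoid it; the article promises neither.

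The sizes are worst cases: about 8% from covariates with baseline OKS kept, 13% for any of three visits, and 16% with the average and interaction added. The 8% rests on assumed correlations; the other two vary little across correlations 0.2 to 0.8. The mismatch between Table 2 and the analysis model needs no such assumption about behaviour: it follows from reproducing the table.

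**What to change.** Before any unblinded analysis, in the protocol or SAP:

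- Delete the clause that puts the covariate assessment ahead of the final model.
- Fix the primary covariates as baseline OKS, site (the randomisation stratum, kept in every model) and sex. Run other covariate sets only as supportive sensitivity analyses.
- Do not use the SMI as a baseline covariate in the primary model, since it is collected only at week 0.
- Name one primary contrast, for example the adjusted OKS difference at week 12, the end of the active intervention, with weeks 52 and 0 secondary. Another contrast would protect the error rate equally well if fixed in advance.
- Restate the sample-size basis for that contrast.

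The cost is mostly wording, but not entirely. A week 12 test adjusted for baseline needs about 315 rather than 262 at correlation 0.5. That is within the expected maximum of 320 but leaves almost no margin, and at correlation 0.2 it would exceed it (403). A benefit seen only at week 52 would become a secondary finding.
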